## Abstract

**Background:**

It has been discussed whether the relationship between a patient on sick leave and his/her general practitioner (GP) is too close, as this may hinder the GP’s objective evaluation of need for sick leave. Independent medical evaluation involves an independent physician consulting the patient. This could lead to new perspectives on sick leave and how to follow-up the patient.

**Methods/design:**

The current study is a randomized controlled trial in a Norwegian primary care context, involving an effect evaluation, a cost/benefit analysis, and a qualitative evaluation. Independent medical evaluation will be compared to treatment as usual, i.e., the physicians’ and social insurance agencies’ current management of long-term sick-listed patients. Individuals aged 18–65 years, sick listed by their GP and on full or partial sick leave for the past 6 months in Hordaland county will be included. Exclusion criteria are pregnancy, cancer, dementia or an ICD-10 diagnosis. A total sample of 3800 will be randomly assigned to either independent medical evaluation or treatment as usual. Official register data will be used to measure the primary outcome; change in sickness benefits at 7, 9 and 12 months. Sick listed in other counties will serve as a second control group, if appropriate under the “common trend” assumption.

**Discussion:**

The Norwegian effect evaluation of independent medical evaluation after 6 months sick leave is a large randomized controlled trial, and the first of its kind, to evaluate this type of intervention as a means of getting people back to work after long-term sickness absence.

**Trial registration:**

ClinicalTrials.gov NCT02524392. Registered June 23, 2015.

## Background

Long-term sickness absence (LTSA) may lead to exclusion, weakening of economic independency and create dependency of health services, welfare services and/or social welfare. The majority of individuals with illness and disease do not need any assistance to return to work (RTW) after a period of sick leave [1, 2]. However, approximately 6.5% will still receive sickness benefits after 6 months [3].

In Norway, 330 individuals reach 6 months of uninterrupted sick leave every day. For these individuals, work disability may lead to disability pension [3]. Amongst 15 OECD countries, Sweden and Norway had the highest percentage increase in people between 20 and 64 years on disability pension, from 1980 to 2007/2008 [4]. This is a negative trend, because very few return to work after having received disability pension [3].

The Norwegian Labor and Welfare Administration (NAV) is the public welfare agency in Norway. It is responsible for a third of the state budget, administering state and municipal welfare agencies, including sickness benefits, pensions, unemployment benefits and social security benefits. Workers are entitled to sickness benefits from NAV if they have been in paid work for the last 4 weeks before the sickness incident. In general, employees receive 100% of their salary (up to 6 G = 555,456 NOK, approx. $ 67,501 in 2016) in sickness benefit from the first day of reported sick and up to 1 year. The employer pays for the first 16 days of a sick leave period, and thereafter NAV covers the disbursement.

The current sickness absence management is organized by NAV. Within 4 weeks from the sick leave starts, the employer is supposed to create a follow-up plan and within 7 weeks arrange a meeting with the sick listed employee. NAV and/or the GP may be invited. The goal of this meeting is to find solutions for RTW, secure dialogue and update the follow-up plan. The employer has to provide work-related activity within the first 8 weeks of sick leave. At 26 weeks of sick leave, NAV arranges for a second meeting, where the person on sick leave and the employer are obliged to participate. The purpose is to find solutions for RTW and to secure a shared view of responsibility and time line.

Sick leave can be graded from 20 to 99% independent of the proportion of employment; full or graded. If the employee does not RTW after 1 year, he or she may receive a transition benefit, which has an upper limit of 4 years. NAV’s general goal is to have more people working and fewer on benefits.

The GP is an important stakeholder, issuing 70% of all sickness certificates in Norway [5]. Most GPs in Norway are self-employed, but are registered on a public list-based GP-scheme with a contract through the local authorities. GPs have no direct financial incentives regarding the length of their patients’ sick leave. Since the GP-scheme entitles all citizens to have a personal GP, the GP is assigned an important role in RTW efforts. Citizens can change GP twice a year. The GPs are reimbursed by a fixed yearly allocation of 380 NOK per patient on the GP-scheme and the average GP list size is 1200 people [4, 6]. Additional reimbursements include consultation fees from patients and the health authorities, based on fixed tariffs.

The patient-GP relation is discussed as problematic by several interests [7]. It is debated whether the public list-based GP-scheme has increased the competition between GPs, and made them more concerned with keeping patients satisfied, than with being strict gatekeepers [8, 9].

Independent medical evaluation (IME) involves an independent physician consulting the patient. It is traditionally requested by insurance companies, attorneys, case managers, and employers who want to establish “estimated” physical capacities, degree of disability, and the reason for work disability [10]. It is also used when there is uncertainty around the functional status and/or the employee’s rehabilitation potential. Ethical and legal issues of IMEs have been discussed, especially the detached relationship between the IME doctor and a vulnerable patient [11].

IME is not commonly used in Norway. The most similar parallel to an IME in a Norwegian context is when NAV is unsure about the GP’s evaluation of the patient’s rights to disability pension and work assessment allowance. A physician employed by NAV then looks at the patient’s medical records and makes recommendations about imbursements. However, this procedure is usually introduced when a patient’s sick leave reaches 1 year. The purpose and organization of the IME of this RCT is outlined below.

In this paper we present the protocol for an ongoing RCT, which aims to explore whether an IME at 6 months of sick leave increases the RTW rate of long-term sick listed patients, compared to the current management of these patients.

## Methods/design

### Aims and objectives

The main aim of this study is to evaluate the effect of IME compared to TAU. The intervention is given to patients after 6 months of continuous sick leave (full or graded sick leave). The IME is conducted by specially trained GPs, performing the IME consultation at their own GP practice in the Norwegian county Hordaland. The following questions will be addressed:Is IME more effective than TAU in getting people back to work after 6 months of sick leave (measured in sick leave grading and length of absence)?Does IME affect sick leave in the Hordaland county control group, compared to sick listed in other control counties, appropriate to comparison?Is IME cost-effective compared to TAU from a societal perspective?How is the intervention affecting the involved stakeholders?

### Outcome measures

The primary outcome is change in sickness benefits at 7, 9 and 12 months. This will be identified through register data from NAV, The Norwegian Health Economics Administration (HELFO), and Statistics Norway.

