As a framework for themes addressed in the IME consultation, the IME physician use a report form. Before meeting the patient, the IME physician prepares for the consultation by starting to fill out the report form with background information from the NAV database and the GPs summary. The IME report includes the following information:Name of IME physicians, date of consultation, name of patient, national identity number and a check box for whether the patient did meet or not for the IME consultation.Name of the responsible NAV office, name of the patient’s GP and a check box for whether the GP did send a medical summary or not in advance of the IME consultation.Brief background information of the patient’s case history: Date of when the current sick leave started, any specialist report enclosed and grade of sick leave at the time of the IME.Information from the patient on work-related actions carried out during the current sick leave period (partial work, “a faster RTW” - actions, dialogue meetings, other work-related actions).The patient’s resources towards RTW (having an employer, type of occupation, type of work tasks, manageable work tasks for the time being, manageable work tasks if adjustments at the workplace, manageable tasks at home).The patient’s own descriptions of why the work ability is reduced related to medical reasons (somatic, mental, cognitive), practical reasons (waiting for medical elucidations or treatment), specific work tasks at the current work place (tasks that can be done or not, and possibilities of adjustments), work tasks at the labor market in general (unemployed, competences).The patient’s own thoughts about RTW (full or partial), answered on a six-point check box (within a month, within 3 months, within the first year of sick leave, later, RTW is not likely (expected), no thoughts about RTW).The IME doctors evaluation of RTW (full or partial): What is the most important medical barrier for RTW (somatic, mental, cognitive factors)? What is the most important practical barrier for RTW? What is the mort important cognitive barrier for RTW? What is the most important barrier for RTW at the current workplace? Will a change of workplace with similar work tasks make it easier to RTW? Will a change of workplace with new work tasks make it easier to RTW?The IME doctor’s suggestion of actions, which must be justified (explained): Additional medical/psychological elucidation, additional medical/psychological treatment, actions/adjustments at the work place (contact NAV/employer), practical actions (job search, social security benefits), change of work place, dialogue meeting or other actions.The IME doctor must state whether sufficient and adequate actions have been accomplished until the current point of time.The IME doctor must suggest grade of further sick leave from the date of consultation (0–100%).The IME doctors concluding remarks, elaborations and summing up.

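### The 12-month primary reading of sickness benefit falls on the general 1-year benefit limit, so ended entitlement can look like return to work; at 7 and 9 months the outcome is a usable but imperfect proxy

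*Protocol article*

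**What the plan says.** The Outcome measures section of the protocol article reads: "The primary outcome is change in sickness benefits at 7, 9 and 12 months". It gives no scale, event or direction for the change.

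The aim is worded as return to work. The Background says that the trial "aims to explore whether an IME at 6 months of sick leave increases the RTW rate of long-term sick listed patients". The first question under Aims and objectives concerns "getting people back to work after 6 months of sick leave (measured in sick leave grading and length of absence".

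The Background also describes the benefit. As a general rule, employees are paid "in sickness benefit from the first day of reported sick and up to 1 year". It continues: "If the employee does not RTW after 1 year, he or she may receive a transition benefit, which has an upper limit of 4 years". Among the schemes that the welfare agency (NAV) administers it lists several kinds, "including sickness benefits, pensions, unemployment benefits and social security benefits", so leaving one need not mean leaving all.

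The only concrete event is in Sample size calculation: being off sickness benefit at 7 months among workers sick listed for 6 months, with 15% in controls and 18% under independent medical evaluation (IME). This also shows that months are counted from the start of sick leave. Participants, recruitment, inclusion and exclusion admits people with and without an employer.

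**The concern.** Twelve months from the start of sick leave is the 1-year limit. At that reading a person can be off sickness benefit because they returned to work or because entitlement ran out, and the outcome as worded does not separate the two. Exhaustion works by rule in both arms. It therefore adds exits unrelated to the intervention, pulls the arms together and can hide a real effect.

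At 7 and 9 months the limit has not been reached in a continuous spell, so the problem there is smaller and of another kind. A move from sickness benefit to another income-replacement benefit satisfies the planning event although nobody has gone back to work. Including people without an employer makes this possible. If such moves differed between arms, part of an observed gain would be transfer and not work.

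At stake is whether one of the three primary readings can answer the main question, and how a positive result at the other two may be worded.

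**Working it through.** **Step 1. Reproduce the plan's own figure.** Inputs from Sample size calculation: p1 = 0.15, p2 = 0.18, 5% significance with only a positive effect expected (one-sided, z = 1.645), power 80% (z = 0.842). With pooled variance under the null and p̄ = 0.165:

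n = [1.645 × √(2 × 0.165 × 0.835) + 0.842 × √(0.15 × 0.85 + 0.18 × 0.82)]² / 0.03² = 1892 per group.

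This equals the stated 1892. A two-sided test would give 2402, so the stated figure is one-sided. The power calculation is thus tied to the event of being off sickness benefit at 7 months. No 12-month rate is given.

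**Step 2. Place the time points against the limit.** Sick leave starts at month 0 and the primary readings are at months 7, 9 and 12. The general limit is 1 year, which is month 12. Months 7 and 9 lie inside the entitlement period of a continuous spell. Month 12 lies on its edge, and the article does not say whether status is read just before or just after it.

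**Step 3. Effect of exhaustion at 12 months.** The documents give no rates, so these inputs are assumptions: control return to work c of 50%, 60% or 70%; true gain d of 3 points; and a share e, equal in both arms, of those not back at work whose entitlement has already ended when status is read.

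- Control share off sickness benefit: c + (1 − c) × e
- IME share off sickness benefit: (c + d) + (1 − c − d) × e
- Difference: d × (1 − e)

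Example with c = 0.60 and e = 0.5: control 0.60 + 0.40 × 0.5 = 0.800; IME 0.63 + 0.37 × 0.5 = 0.815; difference 0.015.

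Power with 1892 per group, one-sided 5%:

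| Share exhausted e | Difference shown (points) | Power, c = 50% | c = 60% | c = 70% |
|---|---|---|---|---|
| 0 | 3.00 | 58.0% | 59.9% | 65.5% |
| 0.25 | 2.25 | 41.8% | 45.3% | 51.7% |
| 0.5 | 1.50 | 28.5% | 31.7% | 37.3% |
| 0.75 | 0.75 | 17.4% | 19.4% | 22.7% |
| 0.9 | 0.30 | 11.2% | 12.2% | 13.8% |
| 1 | 0 | both arms at 100%, no information | same | same |

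The first row is already below 80%, because the assumed control rates have larger variance than the planned 15%. The loss due to exhaustion is the fall from that row downwards.

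**Step 4. Effect of transfers at 7 or 9 months.** Let g be the share of an observed 3-point gain (15% against 18%) that is transfer to another benefit. The true gain in return to work is 3 × (1 − g) points:

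- g = 0.25: 2.25 points
- g = 0.5: 1.5 points
- g = 1: 0 points

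The outcome shows 3 points in every case. The documents give no value for g, so this marks the range and is not an estimate.

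**The case against.** The strongest defence has four parts.

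First, the limit is stated as a general rule for employees and as a maximum. A reader might infer that benefit stops at 1 year for everyone and that the 12-month contrast must be zero. The text does not support that: zero needs e = 1, and e depends on whether status is read just before or just after the limit. This stands against the absolute claim. It does not remove the problem, because the reading is still placed where its meaning depends on an unstated detail.

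Second, a reader might infer that the protocol scores a transfer to another benefit as success. Outcome measures defines no success event; the binary event appears only as the 7-month planning basis. A condensed article may leave the coding of transfers to the full protocol or analysis plan. This stands as a caution on wording. But the article does fix which benefit is counted and at which months, and those two choices create the conflict at 12 months.

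Third, a reader might infer that the outcome does not measure return to work at all. Aims and objectives ties return to work to sick leave grading and length of absence, which are sickness-absence measures, and grading can register partial return. The Background also places the transition benefit after 1 year, and NAV's record review of rights to disability pension and work assessment allowance usually at about 1 year. Transfers at 7 and 9 months may therefore be few. This stands: the two earlier readings are informative proxies, and 7 months is the comparison used for sample size.

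Fourth, a reader might infer that the IME itself raises transfers in one arm, because the report form offers "practical actions (job search, social security benefits" among its possible suggestions. That is speculation. It is one entry in a list, the patient's own general practitioner keeps responsibility for follow-up and certificates, and both arms receive the usual follow-up. The documents show a possible route and no effect.

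**Conclusion.** The point holds, mainly at 12 months. Followed as written, the last primary reading can record ended entitlement as improvement, against the return-to-work aim. This is a badly placed and too narrowly defined reading, and not only missing detail. The visible 12-month difference is the true one multiplied by (1 − e): 3 points become 1.5 if half of those still off work are exhausted, 0.3 if 90% are, and 0 if all are. Power falls from 58–66% with no exhaustion to 29–37% at one half and 11–14% at 90%. These figures rest on assumed control return-to-work rates of 50–70%, a true 3-point gain and equal exhaustion in both arms; none comes from the documents.

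At 7 and 9 months the conclusion is weaker. Sickness-benefit status is usable but includes any move to another benefit, at a rate that the documents do not give. The stated 1892 per group is reproduced, and its arithmetic is not in question.

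**What to change.** Amend the outcome definition as follows:

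- At all three time points, count receipt of transition benefit, disability pension, unemployment benefit or another income-replacement benefit as not returned to work.
- Read the last time point just before the 1-year limit, or keep 12 months only with this combined-benefit definition.
- Keep sick leave grading in the measure, so that partial return still counts, as Aims and objectives requires. A plain yes/no on any benefit would class a person working part-time on graded sick leave as a failure.
- Report sickness benefit alone as a secondary outcome.

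Fix the definition before outcomes are compared by arm. One limit remains: a person with no benefit and no job would still be counted as returned, and the report should say so.

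The cost is recoding and a few more register variables from NAV, which the Background says administers these schemes. The recoding itself needs no more participants. The 15% planning rate must be re-tabulated and the power rechecked. The direction of change is not known in advance: excluding recipients of other benefits can only lower the rate, while counting partial return can raise it.

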### Data collection

Data collected throughout the project is saved in NAV’s secure online database. All directly identifiable personal data (name, social security number, address etc.) is replaced by a unique ID-number before data are sent to Uni Research twice during the project period. Complete and objective data are collected from NAV’s national social insurance register, with no loss to follow-up. Administrative costs at NAV, the IME-physicians’ salary, office rent and patient travel costs will be used for the cost/benefit analysis. Information about education level will be obtained from Statistics Norway, which has the responsibility for official statistics in Norway. HELFO, which is a sub-ordinate institution to the Norwegian Directorate of Health, will provide information about the GPs.

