### Study design

This RCT comprises 1) an effect evaluation, 2) a cost-benefit analysis, and 3) a qualitative evaluation. The main focus of the study is the effect evaluation. The cost-benefit analysis is included to evaluate the resources invested in the intervention, compared to the potential economic gain from reduced sickness absence and increased labor market activity. The qualitative evaluation is conducted to gain insight into stakeholder’s experiences.

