### Interventions

The procedure is organized by NAV. By a randomization procedure, eligible participants are allocated to the IME or TAU. The IME procedure is developed in cooperation with the Research Unit for General Practice at Uni Research Health, and NAV.

Two weeks in advance of the IME consultation, NAV sends an appointment notice to the IME participant, and a request to his/her personal GP to send a medical summary to inform the IME physician. The GP is payed a fixed rate for this summary. The IME physician has a total of 2 h for preparation, consultation (30–60 min) and for writing an IME report. The IME report is sent to the patient, the patient’s GP and NAV. The report will primarily serve as a tool for the GP’s continued follow-up of the patient. The IME report provides a second opinion on the patient’s fitness for work or need for continued sick leave, full or graded. The GP may use this evaluation in his/her communication with the patient, particularly if the IME report points at new options for treatment or other initiatives. The GP is responsible for further follow-up actions and sick leave certificates. Both the intervention group and control group receives TAU (regular follow-up in Norway), which is described in the background section. There are no restrictions in participation in concomitant care or interventions during the study.

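### The economic question is posed from a societal perspective, but the listed cost inputs cover only delivering and attending the IME

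*Protocol article*

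**What the plan says.** Aims and objectives poses the economic question as "Is IME cost-effective compared to TAU from a societal perspective". Data collection then states the inputs: "Administrative costs at NAV, the IME-physicians’ salary, office rent and patient travel costs will be used for the cost/benefit analysis". Study design describes the purpose in matching, narrow terms: "The cost-benefit analysis is included to evaluate the resources invested in the intervention, compared to the potential economic gain from reduced sickness absence and increased" labour market activity.

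The Interventions section describes activity beyond those four inputs. NAV sends "a request to his/her personal GP to send a medical summary to inform the IME physician", and "The GP is payed a fixed rate for this summary". The report form asks the IME physician to consider "Additional medical/psychological elucidation, additional medical/psychological treatment" and adjustments at the workplace. The GP may use the report "particularly if the IME report points at new options for treatment or other initiatives". IME physicians are temporarily employed by NAV and attend training sessions of 7, 3 and 4 hours. Both arms receive usual follow-up, and concomitant care is unrestricted.

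HELFO (the Norwegian Health Economics Administration) appears in Outcome measures as one of three register sources. In Data collection its stated contribution is information about the GPs. No source of patients' health-care use is named.

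**The concern.** A societal analysis counts resource use whoever bears it: the welfare agency, the health service, the employer or the patient. The stated inputs cover NAV's spending on the IME and the patient's travel to it. They include no cost of what the IME is meant to set in motion, which is further investigation, treatment and changes at work. These are intended routes to return to work. Counting the gain they produce without their cost compares a broad benefit with a narrow cost.

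The GP summary fee is a separate matter. It is a direct cost of the intervention with no counterpart in the control arm, and it is not named. If it is missed, the cost of IME is understated.

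At stake is the label on the conclusion. An analysis run on these inputs would be reported as societal while answering a question closer to NAV's own.

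**Working it through.** **1. Perspective against inputs.**

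| Cost | Where the article creates it | Arm | Named in Data collection? |
|---|---|---|---|
| NAV administration | Data collection | IME (delivery) | Yes |
| IME physician salary | Interventions | IME only | Yes |
| Office rent | Data collection | IME only | Yes |
| Patient travel | Data collection | IME only | Yes |
| GP summary fee | Interventions | IME only | No; could sit under NAV administration |
| Training, 7 + 3 + 4 = 14 h per physician attending all sessions | Interventions | IME only | No; could sit under salary or administration |
| Further assessment and treatment | Interventions (report form, GP follow-up) | Both, amounts may differ | No |
| Workplace adjustment | Interventions (report form) | Both, amounts may differ | No |

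The last two rows fit under none of the four headings. That is the mismatch, and it needs no arithmetic.

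**2. The design effect, used as a yardstick.** The article gives no cost or net-benefit figure. Its only design figure is in Table 1, scenario 3: 15% against 18% not receiving benefits at 7 months, 1,892 per group. It reproduces with a one-sided 5% test, 80% power and no continuity correction:

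n = [1.645 × √(2 × 0.165 × 0.835) + 0.842 × √(0.15 × 0.85 + 0.18 × 0.82)]² / 0.03² = 1,892.

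This only confirms that 3 percentage points is the effect planned for.

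**3. Scale of the gain.** Background gives a ceiling on yearly sickness benefit of 555,456 NOK, or 555,456 / 12 = 46,288 NOK per month. A 3-point difference is then at most 0.03 × 46,288 = 1,389 NOK in benefit payments avoided per IME participant per month. This is a payment figure used only for scale. Production by people earning above the ceiling could be worth more.

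**4. Scale of the unnamed items.** The documents give no fee, unit cost or rate of care use, so every range below is an assumption.

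- Fee of 500 to 2,000 NOK: 500 / 1,389 = 0.36 months and 2,000 / 1,389 = 1.44 months of that maximum. Over 1,900 IME participants it is 0.95 to 3.8 million NOK. This total is an upper limit, because the report form records whether the GP sent a summary and some participants are exempted.
- Net extra care, low end: 5% of participants × 2,000 NOK = 100 NOK per participant. High end: 30% × 20,000 NOK = 6,000 NOK. That is 0.07 to 4.3 months, or 0.19 to 11.4 million NOK over 1,900.
- Net care avoided: 10% of participants × 2,000 to 20,000 NOK = 200 to 2,000 NOK saved per participant. The sign reverses.

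The unnamed items could matter to a net-benefit result. The size of every component, and the sign of the care component, remain open.

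**The case against.** The strongest reply is that the article condenses a fuller plan. The Data collection sentence does not say that only these costs will be used, and itemised costing often sits elsewhere. That would answer a complaint about missing detail. It does not answer this one: the article states a perspective and a set of inputs, and Study design confines the cost side to resources put into the intervention. Those statements do not fit together.

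Three stronger readings are tempting, and the documents do not support them.

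- *The GP fee and training are left out.* NAV requests the summary and employs the IME physicians, so both items may fall under administration or salary. The list does itemise physician salary separately although NAV is the employer, which weakens the assumption that another payment to doctors is inside administration. Still, the supportable statement is that the fee is not identified. Training cannot be turned into a share of IME physician time either, because the number of physicians is not given.
- *Net benefit is biased in favour of IME throughout.* That follows for the fee and training if they are not counted, because only the IME arm incurs them. It does not follow for care. Usual care is uncosted too, and the IME may add care or replace it.
- *Benefits saved will be counted as the societal gain.* Nothing says so, and Study design already names labour market activity. What remains is a request to keep benefits and production apart.

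It is also fair to say that the economic analysis is not the study's main focus.

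**Conclusion.** The point holds as a mismatch between the stated societal perspective and the stated cost inputs. Health-care and employer costs are outside the list, although the IME is designed to lead to both, and the GP summary fee is not identified. Overstatement of net benefit for IME is conditional on the fee or training not being counted under NAV administration or salary. For uncosted care, neither direction nor size can be derived from the article. Under the assumed ranges, the fee is worth 0.36 to 1.44 months of the maximum benefit payment avoided at the design effect, and care anything from a saving of 2,000 NOK to a cost of 6,000 NOK per participant. These figures show that the items are not obviously negligible; they do not show that a conclusion would change. The primary outcome, randomisation and sample size are unaffected. It should be corrected before the economic results are reported.

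**What to change.** 1. Name the GP summary fee and the IME physicians' training time as IME costs, and state which heading each falls under. This is a wording change.
2. Then choose one of two routes. (a) Keep the societal perspective and add health-care use and workplace-adjustment costs after randomisation, measured the same way in both arms. This needs a further register extract, and the article does not show that HELFO can supply patient-level use; employer costs would need a source or a stated assumption. (b) Restate the analysis as one from the NAV or intervention-cost perspective, and amend the question in Aims and objectives to match. This costs only text, at the price of a narrower conclusion.
3. In any societal analysis, value the gain as production from work (time worked multiplied by wage cost). Show sickness benefit as a transfer, for example in a separate NAV-budget table, so that the two are never added together. This takes modest analysis time.
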